### Data Cleaning and Preprocessing

Data extracted from EHRs may contain many erroneous entries, as the EHRs are designed for clinical use and not explicitly modified for research purposes. This results in a lot of noise, missing values, outliers, and duplicate or incorrect records due to system problems or clerical errors. These issues will be addressed in several ways. First, wholly duplicated entries will be removed. Second, if the vital signs or laboratory test results are outside the normal range, they are considered outliers. All outliers are marked as missing values and are handled by appropriate imputation methods (eg, the mean or median value imputation based on the training data set). Third, a descriptive analysis will be conducted to determine whether the overall percentage and number are within a reasonable range.

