## Introduction

### Background

Across the globe, there is increasing demand for emergency department (ED) services [1,2]. Increased ED visits have resulted in overcrowding and long waiting times [3-5]. Furthermore, adverse patient outcomes have been reported, such as mortality [6], poor patient satisfaction, and high costs [7,8]. As the first layer of emergency care in an ED, triage plays an essential role in assessing and stratifying patients’ risks and ensuring that the critically ill receive appropriate emergency treatment promptly [9].

The triage process is commonly conducted by medical staff based on their own clinical experience, the patients’ symptoms, and basic information obtained from patients during their presentation to the ED. To make this critical step more objective, triage systems have been introduced. Some examples of triage systems include the 5-level Emergency Severity Index [10] in the United States, the Australasian Triage Scale [11] in Australia, and the Patient Acuity Category Scale (PACS) [12] in Singapore. They are simple and easy to use but subjective and static. These scores are based on symptoms, but many critically ill patients may not have apparent symptoms when they arrive at the ED and their conditions deteriorate rapidly during their stay in the hospital. To address this limitation, more dynamic and accurate risk prediction tools are required for better patient monitoring throughout the ED journey [13].

In response to this gap of needs, researchers are interested in developing multivariable predictive models and clinical scores to identify patients in the ED at risk of adverse outcomes such as admission [14,15], death [16], cardiac arrests [17], and intensive care unit (ICU) admission [18]. Models such as these are primarily based on patient information, vital sign instability, changes in laboratory results, and administrative records. However, some parameters may appear similar between high-risk patients and other patients during an ED visit, making the prediction models less accurate.

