#### Proposed Method: Interpretable SERT

SERT consists of 3 scoring algorithms, each tailored to its application at different time points in the ED. On arrival at the triage station, SERT-1 is used to estimate patients’ likelihood of admission (inpatient and ICU) and 2-day mortality. SERT-1 is intended to assess the patient’s immediate urgency based on basic patient information, simple vital measurements, and medical histories readily available during triage. While in the ED, SERT-2 predicts patients’ admission (inpatient and ICU) and 2/7-day mortality using a variety of variables, including laboratory test results, vital signs, ED treatment, diagnosis, and some administrative information. As an extension of the SERT-1 algorithm, SERT-2 incorporates additional variables obtained during ED stay to better predict outcomes. On admission, SERT-3 predicts the likelihood of 7/30-day mortality, ICU transfer, and prolonged length of stay using variables collected in the ED and during the first 24 hours of inpatient stay. In actual clinical implementation, in the case where a patient has incomplete information, SERT will use imputation methods to fill in the missing values before calculating the risk score. In summary, SERT allows for a comprehensive risk assessment and prediction in the ED in a dynamic manner.

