#### Baseline Methods: Traditional Clinical Scores

Several traditional clinical scores will be calculated for performance comparison with the SERT scores. They are the PACS triage system [32], Modified Early Warning Score [44], National Early Warning Score [45], Rapid Acute Physiology Score [46], Rapid Emergency Medicine Score [47], and Cardiac Arrest Risk Triage [48].

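### The cleaning rule uses the normal range to find erroneous entries, so read literally it also discards true abnormal vital signs and laboratory results before the SERT scores are built

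*Protocol article*

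**What the plan says.** All references are to the protocol article.

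- **Data Cleaning and Preprocessing** gives the problem to be solved as noise, missing values, outliers and "duplicate or incorrect records due to system problems or clerical errors". The remedy for outliers is: "if the vital signs or laboratory test results are outside the normal range, they are considered outliers. All outliers are marked as missing values". They are then imputed; the mean or median from the training data is offered as an example.
- **Study Cohort and Design** puts outlier removal and missing-value handling on the master data set first. The interpretable framework, and the comparison with clinical scores, machine learning and deep learning, come after that.
- **Proposed Method: Interpretable SERT** has SERT-1 work "based on basic patient information, simple vital measurements, and medical histories readily available during triage" and SERT-2 predict "using a variety of variables, including laboratory test results, vital signs, ED treatment, diagnosis, and some administrative information". SERT-3 uses variables from the ED and the first 24 hours of the inpatient stay, and Table 1 lists vital signs and laboratory tests for both periods.
- **Background** says of prediction models in this field: "Models such as these are primarily based on patient information, vital sign instability, changes in laboratory results, and administrative records".
- **Baseline Methods: Traditional Clinical Scores** states: "Several traditional clinical scores will be calculated for performance comparison with the SERT scores". It does not say whether raw or cleaned values feed those scores.

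**The concern.** The criterion does not match its purpose. A clerical error is a value that cannot be right. A value outside the normal range may well be right, and in an emergency department it is often the reason for the visit. A rule keyed to normality cannot tell the two apart and removes both.

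What is lost is not a random sample. The recorded value alone decides whether it is deleted, so the missingness is not at random. Any imputation model then has only in-range values to learn from, whichever method is chosen. With a mean or median, a patient with a grossly abnormal reading is given a typical one.

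At stake are the physiological predictors of all three scores. AutoScore cuts continuous variables into categories and assigns points to each. If the tails have been emptied, no category is left to carry points for abnormal physiology, and the central category holds a mix of well patients and relocated sick ones.

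**Working it through.** **1. Text check.** Nothing in the article gives the normal range another meaning, exempts true abnormal values or keeps a flag for abnormality. The Limitations section leaves imputation strategies open, but for sparse data, and does not withdraw the deletion rule. The descriptive check listed as the third cleaning step restores no values. The rule therefore stands as written.

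**2. What it touches.** Vital signs and laboratory results at triage, in the ED and in the first 24 inpatient hours. Table 1 lists the Glasgow coma scale among the ED vital readings; if normal were taken as the full score, this predictor would become a constant. Not touched: demographics, mode of arrival, triage class, comorbidities, past utilization, measurement frequency, treatment and diagnosis.

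**3. Size.** The plan has no figure to reproduce, so the following is an illustration in which every input is an assumption.

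- One predictor x in reference-range units, x ~ N(0, 1.3²); normal range ±1.96; n = 300,000; outcome prevalence 2%.
- logit P(outcome) = a + b·x (monotone) or a + b·|x| (U-shaped), with b = 0.5, 1.0 or 1.5.
- Written rule: if |x| > 1.96, replace x by the median of the in-range values.
- Score: five categories cut at the 5, 20, 80 and 95% quantiles, each given its observed risk.

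Expected share deleted: P(|Z| > 1.96/1.3) = P(|Z| > 1.508) ≈ 0.13, as the simulation returned.

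| Risk shape, b | Deleted, all | Deleted, patients with outcome | AUC, uncleaned | AUC, written rule | Fall |
|---|---|---|---|---|---|
| Monotone, 0.5 | 13.0% | 19.6% | 0.642 | 0.595 | 0.047 |
| Monotone, 1.0 | 13.1% | 37.7% | 0.772 | 0.636 | 0.136 |
| Monotone, 1.5 | 13.1% | 58.0% | 0.867 | 0.627 | 0.240 |
| U-shaped, 0.5 | 13.2% | 26.6% | 0.601 | 0.517 | 0.084 |
| U-shaped, 1.0 | 13.2% | 44.0% | 0.713 | 0.542 | 0.171 |
| U-shaped, 1.5 | 13.2% | 62.5% | 0.809 | 0.574 | 0.235 |

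Deleting only values beyond ±6 units gave the same AUC as uncleaned data. That is nearly so by construction: no erroneous entries were put in, and a limit at 6/1.3 = 4.6 SD removes almost nothing. It shows that plausibility limits spare the signal, not how well they catch errors.

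**4. Why category effects are distorted.** Take monotone risk with b = 1.0. Risk among deleted values is 0.02 × 0.377 / 0.131 = 5.8%; among kept values it is 0.02 × 0.623 / 0.869 = 1.4%. The higher-risk group is moved into the central category, whose observed risk rises. Contrasts with that category need not simply shrink towards zero; some could change sign.

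**5. Comparators.** The order of steps in Study Cohort and Design suggests that the clinical scores are calculated after cleaning; the section on those scores is silent. PACS is described under Study Setting as symptom-based, so the rule does not reach it.

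**The case against.** The strongest reply is that this is a slip of wording. The paragraph opens with erroneous entries, the Background relies on unstable vital signs, and the plan includes early warning scores and the tuning of cut-offs. All of that makes sense only if abnormal values survive. A plausible range may well be what the authors meant. This is persuasive about intent, but the sentence says something else, and an analyst following it would delete true values. Leaving the limits for each variable to a fuller document would be no fault in an article; stating the wrong criterion is.

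A second reply is that mean or median imputation is only an example. That is correct, and the plan does not fix the method. It softens the consequence without curing it, because a value that was observed and then discarded still has to be guessed.

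A third is that the illustration is not evidence about this study. This stands in full as to size: the inputs are assumed, only one predictor is modelled, and the predictors that the rule leaves alone are absent. The falls in AUC cannot be carried over to a full SERT score.

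A reader might go further and infer that the rule wipes out everything SERT can detect, or that the comparison with the clinical scores is invalid because those scores lose even more. The documents support neither. Many predictors are untouched, whether the comparators use cleaned data is not stated, and no early warning score was computed here.

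**Conclusion.** The point holds as a rule that is wrong as written and contradicts its own stated aim. Taken literally, it removes the out-of-range part of the vital-sign and laboratory information from SERT-1, SERT-2, SERT-3 and the machine learning baselines, and it distorts category effects. In-range variation and the non-physiological predictors remain. Harm to the comparator scores other than PACS is possible and depends on a choice that the article leaves unstated.

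The size is unknown from the documents. Under the assumed inputs, about 13% of all values but 20% to 63% of the values in patients with the outcome are deleted, and the single-predictor AUC falls by about 0.05 to 0.24. These figures rest on the assumed spread, prevalence, slopes and median imputation, and serve only to show the mechanism. The sentence should be corrected before modelling; the Results section reports that linking and cleaning are under way.

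**What to change.** In Data Cleaning and Preprocessing, define an outlier as a value beyond prespecified physiologically or analytically plausible limits, with a lower and an upper limit tabulated for each variable. Set only those entries to missing and keep abnormal but possible values as recorded. State that the same limits apply to the training and validation cohorts, to both testing cohorts (2019 and 2020), and to the data from which the comparator scores are calculated.

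The cost is one sentence and a table of limits, with no new data. The price is that a few entries that are wrong but plausible will stay in the data set.

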### Variable Construction

Candidate variables have been identified based on expert opinions as well as relevant literature [18,30,34-36]. Moreover, we have sought input from clinicians and informaticians familiar with the raw data to determine which features are feasible to extract and construct from the sources. The general rationale is to include all ED-relevant variables of high quality. Therefore, irrelevant, repeated, or largely missing variables will be excluded. For time-series data (such as laboratory test results and vital signs), the first, last, and average measurements are extracted and constructed for each ED episode. Past health care utilization will be derived per the patient’s medical history.

Table 1 presents a list of high-level constructed variables. These variables are classified into 6 main categories depending on the time frame during which the variables could be collected: past medical history, ED triage, ED disposition, within the first 24 hours of inpatient stay, inpatient discharge, and after inpatient discharge. Variables of patient data include demographics, comorbidities, drug history, presenting vital signs, essential laboratory results, and treatments administered in the ED. There are also nonpatient variables such as ED waiting time from triage to consultation, ED boarding time (from consultation to ED disposition), patient load in the ED (number of other patients registered in the ED at that time), time of the day, and day of the week.

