**Information collected at ED disposition**			
	ED vital signs	ED vital signs	Vital measurement frequency and major ED vital readings: pulse, respiration, fraction of inspired oxygen, SpO_2_, systolic BP, diastolic BP, temperature, pain level scale, Glasgow coma scale, alert (extracted from physical notes)
	ED laboratory	ED laboratory	Laboratory measurement frequency and major laboratory test results: potassium, creatinine, sodium, bicarbonate, albumin, creatine kinase-MB (mass), creatine kinase, prothrombin time, N-terminal pro–B-type natriuretic peptide, C-reactive protein
	ED consultation and treatment	ED consultation, ED treatment	Services provider, consultation waiting time, ED location, length of consultation, resuscitation, major emergency surgeries, pre-selected major ordering
	ED allergy	ED allergy	Major allergy types and reasons, severity
	ED disposition and diagnosis	ED disposition, ED diagnosis	Disposition type, major primary diagnosis, secondary diagnosis (eg, trauma)
	Outcomes	ED disposition, ED root table	Admissions, mortality within ED, direct transfer to ICU

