#### Baseline Methods: Black Box Machine Learning Models

Additionally, several machine learning techniques will be compared as baselines for predictive modelling. Of the many machine learning algorithms, we will apply the following popular ones as examples.

Random forest [49]: As the most commonly used tree-based prediction tool, its R package “RandomForest” will be used for model fitting. The parameters will be selected based on recommendations made in previous literature [50,51], where *ntree*= 100 and *mtry* is the principal square root of *m* (*ntree* number of trees grown; *mtry*: number of variables randomly sampled as candidates at each split).Least absolute shrinkage and selection operator [52]: As a penalized regression technique, it is another popular method used in clinical modelling. It is a regression-based method that employs a regularization process for variable selection to increase the statistical model’s predictive accuracy and interpretability. In our study, its regularization rate will be optimized through 10-fold cross-validation.Deep learning [53]: As a branch of the machine learning field that uses deep neural networks, deep learning was initially widely adopted for computer vision and image understanding before being used for medical image analysis. More recently, researchers have begun to explore deep learning for EHR analysis [54,55]. We are particularly interested in applying deep learning algorithms for adverse event prediction, drawing on the rich sources of EHR data, as described earlier. Using the PyTorch library, we will construct a long short-term memory network [56]. In addition, a multilayer perceptron [57] will be used in conjunction with long short-term memory to learn nontemporal data.

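### Summarising each ED vital-sign and laboratory series by first, last and average loses the depth and timing of a transient abnormality; minimum and maximum should be added as candidates, together with a change to the outlier rule.

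*Protocol article*

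**What the plan says.** Variable Construction in the protocol article covers repeated measurements in one sentence. It opens "For time-series data (such as laboratory test results and vital signs" and continues that "the first, last, and average measurements are extracted and constructed for each ED episode". For the ED stay, Table 1 lists "Vital measurement frequency and major ED vital readings" and the same pairing for laboratory tests, so measurement frequency is a further candidate. Neither place names a minimum, maximum, range or slope.

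Two sections explain why data from the stay matter. Background criticises symptom-based triage scales because "many critically ill patients may not have apparent symptoms when they arrive at the ED and their conditions deteriorate rapidly". Proposed Method: Interpretable SERT says that "SERT-2 incorporates additional variables obtained during ED stay to better predict outcomes", and gives the targets: "While in the ED, SERT-2 predicts patients’ admission (inpatient and ICU) and 2/7-day mortality using a variety of variables".

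Two further sections bear on the point. Data Cleaning and Preprocessing treats any vital sign or laboratory value outside the normal range as an outlier, sets it to missing and imputes it. Baseline Methods: Black Box Machine Learning Models says "we will construct a long short-term memory network", and gives the nontemporal data to a multilayer perceptron.

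**The concern.** The three summaries fix the first reading, the last reading and the level, but not how far a value moved in between or when. Two patients with very different courses can therefore have identical values on a measurement, and no model built on these summaries can then separate them on it. SERT-2 is expected to improve on SERT-1 through what is learned during the ED stay, and the depth of an excursion is part of that information.

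The number of readings matters too. The more often a patient is measured, the more a single abnormal reading is diluted in the average. If sicker patients are measured more often, which is plausible but not stated in the article, the dilution is greatest in the patients of most interest.

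A lesser question concerns the LSTM. It needs readings in time order, and the only construction of time-series variables that the article describes is the three-value summary. A comparison of SERT with deep learning reads differently according to which input the network receives.

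**Working it through.** The article gives no figure on this point, so there is none to reproduce. The check is arithmetic on example series. The readings are assumed for illustration: a baseline of 120, a drop of 40, and 3 to 12 readings per stay.

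**1. Transient drop that recovers before the last reading.** With baseline B and one of k readings lower by D:
- first = B and last = B, both unchanged;
- average = B − D/k, so the average keeps a share 1/k of the drop;
- minimum = B − D, the full drop.

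With B = 120 and D = 40:

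| k | First | Last | Average | Share of drop kept in average | Minimum |
|---|---|---|---|---|---|
| 3 | 120 | 120 | 120 − 40/3 = 106.7 | 33% | 80 |
| 5 | 120 | 120 | 120 − 40/5 = 112.0 | 20% | 80 |
| 10 | 120 | 120 | 120 − 40/10 = 116.0 | 10% | 80 |
| 12 | 120 | 120 | 120 − 40/12 = 116.7 | 8% | 80 |

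**2. Different courses, same summaries.**
- 120, 80, 120, 120, 120: first 120, last 120, average 560/5 = 112, minimum 80.
- 120, 107, 107, 106, 120: first 120, last 120, average 560/5 = 112, minimum 106.
- 120, 120, 120, 80, 120: first 120, last 120, average 560/5 = 112, minimum 80.

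The first two series differ in depth and the first and third in timing, yet all three have the same first, last and average. The minimum separates the first two. It does not restore timing.

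**3. Sustained deterioration.** With the second half of the readings at 80, first = 120, last = 80 and average = (120 + 80)/2 = 100 for k = 4, 6 or 10. The fall of 40 is fully visible in last against first, so nothing of its depth is lost.

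**4. Interaction with the cleaning rule.** Take 120, 120, 80, 120, 120 and assume, for illustration only, a normal range of 90 to 140.
- Before cleaning: average 560/5 = 112, minimum 80.
- After 80 is set to missing: average of the remaining readings 480/4 = 120, minimum 120.

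Read literally, the rule removes the excursion before any summary is formed. Adding a minimum would then recover nothing.

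**The case against.** A reader might infer three stronger points, and the article does not support them.

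- *That the summaries hide mid-stay deterioration in general.* Step 3 shows that they do not: a deterioration still present at the last reading is visible. Even a transient one is diluted in the average, not erased.
- *That catching such deterioration is SERT-2's stated purpose.* Its stated targets are admission (inpatient and ICU) and mortality at 2 and 7 days. Deterioration appears as motivation, and Background places it more widely: "their conditions deteriorate rapidly during their stay in the hospital". The Significance section speaks of instability appearing later, in the ward, which is after the ED window.
- *That the LSTM is left with no time sequence.* Nothing confines it to the summaries. Assigning the nontemporal data to the perceptron implies temporal input for the LSTM, the source tables were extracted, and a condensed article may leave the exact input to the full protocol.

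It can also be argued that other candidates carry part of the signal. Table 1 includes measurement frequency, resuscitation, ED location and selected orders, and an episode that was noticed and treated may leave traces there. The candidates were chosen with clinicians, and parsimony is a design aim. Finally, the example readings are assumed and show no effect on the area under the ROC curve.

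These arguments limit the size of the point. They do not remove it: depth and timing of a recovered excursion are discarded by a stated choice, the proxies are indirect, and candidates that add nothing can be dropped by AutoScore itself. The objection that minimum and maximum would fail under the present cleaning rule is correct, and the fix has to include that rule.

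**Conclusion.** The point holds in a limited form. First, last and average discard the depth and timing of an ED abnormality that recovers before the last reading. The average keeps 1/k of a drop seen in one of k readings, which is 33% at three readings and 8% at twelve. The loss is nil with a single reading, and the depth of a sustained deterioration is retained.

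The shares follow from arithmetic for any size of drop. They assume that one reading is affected, that the others stay at baseline, and that the abnormal reading survives cleaning. How often such courses occur, and how much prediction would improve, cannot be derived from the article. The case for change rests on the study's own motivation and on the low cost. It is a worthwhile improvement to the candidate set and does not invalidate the planned analysis.

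The LSTM part is a request for clarification only.

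**What to change.** 1. In Variable Construction, add the minimum and maximum of each ED vital-sign and laboratory series, taken up to the time at which the score is calculated, to the candidate variables. Let AutoScore module 1 (ranking) and module 4 (parsimony plot) decide whether they stay.
2. In the same revision, change Data Cleaning and Preprocessing so that only physiologically implausible values are set to missing, not every value outside the normal range. Without this, step 1 recovers little.
3. As a secondary clarification, state that the LSTM takes the time-ordered readings up to the same prediction time, and note that its inputs then differ from those of SERT when the two are compared.

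Cost: two extra columns per series from tables already extracted, a defined plausibility range per measurement, and the time-stamped rows kept for the LSTM. No new data are needed. There is a small downside: more correlated candidates enter the random forest ranking, and extremes are more sensitive to entry errors than averages, so the plausibility check must be applied before they are formed.
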